### Adverse and serious adverse events

Any manifestation of symptoms or conditions, laboratory parameter alteration, or recurrence or aggravation of existing co-morbidity that correlate with the use of an investigational or medicinal substance or product constitutes an adverse event (AE). A serious adverse event (SAE) is defined as an AE that is life threatening and necessitates hospitalization and/or prolonged medical treatment until stabilization. The occurrence of all events that can be classified as adverse will be recorded and its clinical course will be followed until resolution and stabilization. Events associated with the primary diagnosis, the surgical procedure itself, or complications related to the palliative chemotherapy will not be registered as SAEs unless deemed so by the investigator. All SAEs will be documented and reported to the PI (author PS) within 24 hours or during the following calendar working day, at the latest. The PI will then report the newly documented SAEs to the ethics committee and the investigators. Apart from meteorism, which is a common phenomenon associated with cabbage, a very low risk for AEs is expected during this trial.

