In a review published in 2007, the American Institute for Cancer Research (AICR) drew attention to the benefits of increased cabbage consumption in PDA patients [15]. These results were not restricted to the pancreas, as two recent epidemiological, prospective nutrient studies demonstrated significant inhibition of metastases seeding in patients with prostate cancer [16,17]. Kirsh, *et al*. observed the significantly decreased risk of extra-prostatic manifestation of prostate cancer (stage III or IV tumors) correlated with an increase in the consumption of cruciferous vegetables, in particular broccoli which is rich in sulforaphane and quercetin (*P* = 0,02) [16]. The benefits inferred by sulforaphane, which is derived from mustard oil, and its inactive glycoside precursor, glucoraphanin (present in high concentrations in broccoli and its sprouts), have been thoroughly investigated [18,19]. Sulforaphane is believed to target CSCs through the downregulation of NF-κB [18]. This observation was first discovered in PDA and has also been confirmed for breast and prostate cancer [20,21]. Consequently, these substances may serve as an alternative treatment option for PDA; by exhausting pancreatic CSCs, the tumor sensitivity to chemotherapeutics, such as sorafenib, gemcitabine, cisplatin, doxorubicin, and 5-fluorouracil, may be significantly improved [20,22,23].

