### Outcome measures

Serum levels of the pancreatic tumor markers carbohydrate antigen 19-9 (CA19-9) and carcinoembryonic antigen (CEA), and routinely performed cross-sectional imaging (computed tomography or magnetic resonance imaging), will be monitored and assessed as parameters for evaluating disease status. Staging examinations will take place every three months after study inclusion during the treatment course with cytoreductive chemotherapy (Figure 1). The total concentration of isothiocyanates (sulforaphane) in urine will serve as a monitoring parameter for the evaluation of patient compliance. Additionally, the overall survival rate will be documented.To evaluate the quality of life of the study participants, questionnaires (European Organisation for Research and Treatment of Cancer (EORTC) Quality of Life Questionnaires (QLQ-PAN26, QLQ-C30) will be completed at every follow-up visit (3, 6, and 12 months after patient inclusion), in addition to the evaluation of a patient diary kept to document the regular intake and amount of the test substances, and any observable side effects (adverse or otherwise) (Figure 1). If outcome differences between the verum and the placebo groups are detected after completion of the POUDER trial, statistical analyses will be performed in order to generate a hypothesis for a confirmatory trial on this topic.

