With regard to sulforaphane, its modus operandi is believed to be as an indirect antioxidant that helps to protect healthy cells from oxidative damage and reduce the short- and long-term harmful effects of cancer treatment [42]. However, concern has been raised that antioxidant supplements may also protect tumor cells during chemotherapy, thereby compromising treatment efficacy [42,43]. This has resulted in controversy over the guidelines for the use of vitamin supplements during cancer treatment. This issue was examined in an experimental human PDA xenograft model in mice. In this setup, sulforaphane did not protect tumor cells; instead, it increased the effect of gemcitabine, cisplatin, doxorubicin, 5-fluorouracil, sorafenib, and TRAIL [20,22,23,27].

In closing, the POUDER trial is the first clinical pilot trial to test the feasibility of an intake of freeze-dried broccoli sprouts as an additive of palliative chemotherapy in surgically non-resectable, advanced pancreatic cancer. Depending on the results of this pilot trial, a hypothesis for a confirmatory trial in the field will be generated and a consecutive RCT is planned.

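### The SAE definition omits death, joins its criteria with 'and', and leaves disease and chemotherapy events to unguided discretion, so serious harm from an altered chemotherapy effect may go unregistered

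*Protocol article*

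**What the plan says.** Three rules stand together in the protocol article under Adverse and serious adverse events.

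- **What counts as an AE.** Symptoms, laboratory changes and worsening co-morbidity count if they are of the kind "that correlate with the use of an investigational or medicinal substance or product constitutes an adverse event (AE").
- **What counts as an SAE.** "A serious adverse event (SAE) is defined as an AE that is life threatening and necessitates hospitalization and/or prolonged medical treatment until stabilization".
- **What is kept off the SAE register.** Events of the primary diagnosis and of the surgical procedure are exempt, and "complications related to the palliative chemotherapy will not be registered as SAEs unless deemed so by the investigator".

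The same section says: "The occurrence of all events that can be classified as adverse will be recorded", with follow-up of their course. SAEs go to the principal investigator within a day or by the next working day, and from there to the ethics committee and the investigators. No such route is stated for other AEs.

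Elsewhere, the Abstract lists adverse effects among the assessments. Background says that with the supplement "the tumor sensitivity to chemotherapeutics, such as sorafenib, gemcitabine, cisplatin, doxorubicin, and 5-fluorouracil, may be significantly improved". The Discussion acknowledges the opposite worry: "concern has been raised that antioxidant supplements may also protect tumor cells during chemotherapy, thereby compromising treatment efficacy".

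**The concern.** A safety definition should catch the harms that the treatment could plausibly cause. Here the intended mechanism is a change in the effect of chemotherapy. If it works in normal tissue as well as in tumour, the harm is more chemotherapy toxicity. If the antioxidant worry is right, the harm is faster progression. These are complications of chemotherapy and events of the primary diagnosis, the two groups that are off the SAE register by default.

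The investigator can put an event back, but the article gives no criterion for doing so. A blinded investigator looking at one patient cannot tell chemotherapy toxicity that the supplement has amplified from toxicity that would have occurred anyway. Only full registration and a comparison of the arms could show an excess.

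At stake are the sensitivity of the SAE comparison and the timeliness of reporting to the principal investigator and the ethics committee. A short SAE list could be taken as reassurance when a confirmatory trial is designed.

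**Working it through.** The protocol states no SAE rate, and its 40 patients rest on no calculation, so there is no figure to reproduce. The main check is to follow the rules as written.

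**Step 1. Apply the definitions to event types.**

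| Event | AE? | SAE as written? |
|---|---|---|
| Hospital admission, substance-related, not life threatening | Yes | No: the life-threat condition fails |
| Life-threatening chemotherapy complication with admission | Yes: chemotherapy is a medicinal substance | Not by default; only if the investigator so decides |
| Complication of progression with admission | Unclear: needs a link to a substance | Not by default; only if the investigator so decides |
| Death | Only if linked to a substance | Not because it is a death |

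The SAE sentence joins its first two conditions with a plain 'and', while 'and/or' appears later in the same sentence. The literal reading is therefore that both a life threat and a need for hospital care or prolonged treatment are required. The reference to stabilisation describes a patient who survives.

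**Step 2. How many deaths are at issue (illustration).** Inputs: 40 patients (Methods/Design), one year of follow-up (Trial interventions), and a median survival of 4 to 6 months (Background; a general figure for the disease, not a planning assumption of this trial). Assumption: exponential survival.

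Deaths by 12 months = 40 × (1 − 0.5^(12/median)).

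- Median 4 months: 40 × (1 − 0.125) = 35
- Median 6 months: 40 × (1 − 0.25) = 30
- Median 9 months (assumed): 40 × (1 − 0.397) = 24.1
- Median 12 months (assumed): 40 × (1 − 0.5) = 20

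None of these is an SAE by virtue of being a death.

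**Step 3. How far the SAE count depends on the override (illustration, all rates assumed).** Let r be the share of patients with an otherwise serious event, a the share of those events attributed to disease or chemotherapy, and d the share of attributed events that the investigator nevertheless registers. Then q = r × [(1 − a) + a × d], the expected count is 40q, and P(at least one) = 1 − (1 − q)^40.

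With r = 0.40 and a = 0.95:

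| d | q | Expected SAEs in 40 | P(at least one) |
|---|---|---|---|
| 0 | 0.020 | 0.8 | 0.55 |
| 0.25 | 0.115 | 4.6 | 0.99 |
| 0.50 | 0.210 | 8.4 | above 0.99 |
| 1 | 0.400 | 16 | above 0.99 |

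With no override, r from 0.20 to 0.60 and a from 0.80 to 0.95, the expected count runs from 0.4 (r = 0.20, a = 0.95; P = 0.33) to 4.8 (r = 0.60, a = 0.80; P = 0.99).

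The same clinical events can therefore give a nearly empty SAE list or a full one, depending on a decision for which the article gives no rule.

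**The case against.** The strongest reply is that the events lose the SAE label by default but not their place in the data.

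- The exemption is limited to SAE registration and carries an override. The AE definition covers any medicinal substance, so chemotherapy reactions can be AEs, and all AEs are recorded. A diary also captures "any observable side effects (adverse or otherwise"), and Fisher tests are planned for categorical parameters.
- Deaths are documented and compared by arm with Kaplan-Meier curves and a log-rank test. Deaths in the first six months are expressly kept. Tumour markers and available imaging bear on progression.
- Investigators, patients and assessors are blinded, so attribution and override are decided without knowledge of the arm.
- 'Correlate' might mean association in time rather than cause.

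Much of this stands. A reader might infer that the trial would show almost no SAEs whatever happened, that every chemotherapy-related admission is lost, or that adverse effects cannot be validly compared between the arms. The documents support none of these. The override exists and its frequency is unknown, and blinding makes the loss one of sensitivity rather than bias between arms. Nor do the deaths disappear, since they are analysed as survival.

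The reply does not close the gap. AEs that miss the SAE label have no stated prompt route to the principal investigator or the ethics committee. Progression events do not clearly meet the AE definition. A survival curve is an outcome analysis, not event reporting. Moreover, under Randomization and blinding, patients who withdraw by choice at month 6 have all their data removed, and patients in the broccoli sprout group whose urine shows that they did not take the capsules daily are discarded. No exception for safety data is stated, so patients who stop capsules because of toxicity could leave the record. Finally, even if 'correlate' means timing, the SAE definition and the exemption are untouched.

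**Conclusion.** The point holds as a fault in stated rules, not as missing detail. Followed literally, the definitions under-register serious events and keep them out of prompt reporting. The events most affected are those that the trial's own rationale makes most plausible. AE recording and the survival analysis are a partial backstop.

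Its size cannot be fixed from the article. The range of 0.8 to 16 registered SAEs rests wholly on assumed event and attribution shares, and shows only how much depends on the override. The 30 to 35 deaths assume exponential survival at a background median, would be about 24 or 20 at medians of 9 or 12 months, and are deaths that the trial still analyses. They do not measure lost data.

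A reader might also infer a breach of ICH-GCP, to which Assurance of quality commits the trial. The article does not reproduce that guideline's definition, so the conclusion does not rest on it.

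**What to change.** Reword the AE and SAE section and the case report form as follows.

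1. Record every untoward event in both arms from randomisation, whatever its presumed cause, with the blinded causality judgement as a separate field.
2. Make the seriousness criteria alternatives, any one of which suffices: death, threat to life, hospitalisation or its prolongation, lasting disability.
3. Register serious events of the disease and of chemotherapy, and tabulate them by arm with severity.
4. If expected events are to be exempt from anything, limit the exemption to expedited reporting and list those events in advance.

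The cost is protocol and form wording, plus more event documentation. Many events will be registered in this population, but with 40 patients the load is manageable.

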### Assurance of quality

The principles of the International Conference on Harmonisation-Good Clinical Practice (ICH-GCP) guidelines [32], the regulations of the Declaration of Helsinki, [33] and local legal and regulatory requirements will be adhered to at all times during the trial period. Medical confidentiality and accordance with the German Federal Data Protection Act will also be observed [34].

## Discussion

Since ancient times, cabbages and other extracts of the botanic family *Brassicacea* have been used as natural antibiotics and key components of antiviral drugs and antimycotics. Members of the *Brassicacea* family contain glycosides that trigger the release of mustard oils after enzymatical hydrolyzation, in case of physical damage of the plant cells. These mustard oils offer protection against microorganisms and fungi. To date, the bioactive function of more than 120 different mustard oils have been documented [35].

With regard to numerous worldwide studies, an inverse relationship between consumption of cruciferous vegetables (including members of the *Brassicacea* family) and the risk of neoplastic diseases has been observed, namely in colorectal, gastric, lung, breast, prostate, bladder, and endometrial cancers [18,19]. The bioactive phytochemicals, sulforaphane and quercetin have been shown to be potent substances that possess chemopreventive and therapeutic properties beneficial in cancers of the intestine, breast [28,29], prostate [17], and pancreas [20]. Sulforaphane, and its inactive glycoside precursor, glucoraphanin, are present in high concentrations in broccoli and its sprouts [18,19]. Sulforaphane is a potent antioxidant that indirectly eliminates free radicals; by increasing the concentration of glutathione, sulforaphane inhibits the formation and accumulation of carcinogen-induced DNA adducts [18,36], a finding that has been demonstrated in several animal studies [25,26]. Furthermore, sulforaphane is of interest as a new therapeutic anti-cancer substance, based on recent experimental studies in which the compound has been shown to target CSCs in models of pancreatic, breast, and prostate cancer [20,21]. In pancreatic cancer, sulforaphane was shown to exhibit its anti-CSC effect through the downregulation of NF-κB activity, which is usually enhanced in active CSCs [18]. Consequently, sulforaphane might be effective in overcoming the resistance of pancreatic cancer cells to chemotherapy, as underlined by recent experimental studies. These studies show that sulforaphane increases the responsiveness of pancreatic CSCs to sorafenib, gemcitabine, cisplatin, doxorubicin, and 5-fluorouracil [20,22,23].

Another bioactive agent is quercetin, a polyphenol flavonoid commonly found in apples, berries, red grapes, onions, and broccoli, [37] with antioxidant, anticarcinogenic, anti-inflammatory and cardioprotective activities [38,39]. Recent reports describe the possible use of quercetin to inhibit the self-renewal and therapy resistance of pancreatic CSCs by affecting clonogenicity, spheroid formation, and aldehyde dehydrogenase isoform 1 (ALDH1) activity, as well as blocking the signaling pathways involved in apoptosis resistance, proliferation, angiogenesis, NF-κB activity, and epithelial-mesenchymal transition (EMT) [27]. It is most effective in combination with sulforaphane both *in vitro* and *in vivo*, without inducing toxic side effects in mice [27]. These findings emphasize the need for dietary intervention studies to elucidate the therapeutic effects of vegetables rich in sulforaphane and quercetin for more successful treatment of therapy-resistant PDA.

Since 2012 a pilot study has been evaluating the dose-dependent effects of broccoli sprout extract on atypical nevi, as precursor lesions and malignant melanoma (clinicaltials.gov identifier: NCT01568996) in an 18-patient collective. Two other ongoing pilot studies are examining the preoperative administration of broccoli sprout extract in patients with transitional cell bladder cancer undergoing surgery (NLM identifier: NCT01108003) and the additive intake of broccoli sprout extract in patients with recurrent prostate cancer (clinicaltrials.gov identifier: NCT01228084).

From the available studies, it can be noted that there is a positive correlation between the consumption of broccoli and an increased efficacy of chemotherapy [27,40]. However, to date this is not based on high-level evidence trials. The POUDER trial will not interfere with any palliative chemotherapy or targeted therapy as these substances typically do not require any food restrictions. Consequently, patients who participate in PDA trials can simultaneously participate in a broccoli nutritional study. However, compounding effects of the intake of broccoli sprouts might have an influence on the results of any parallel trial due to the potential benefit of their application. The present trial has to be regarded as a test of feasibility. Participation in other treatment schemes - regardless of whether or not standard or study substances are applied - was not defined as a contraindication for inclusion. As patients suffering from tumor diseases are often encouraged to make healthy changes in their lifestyle, other phytotherapies may be expected. Yet, the effects of the chosen high dosage of the broccoli sprout extract will probably overpower the effects of any other nutritional substance.

A possible side effect of high broccoli sprout intake may be meteorism, which is a common phenomenon associated with cabbage consumption. Other effects include the prominence of the rotten-egg odor. During the metabolic breakdown of cabbage in the digestive tract, sulfur in the glucosinolates [41] is converted into the rotten-egg chemical, hydrogen sulfide, by gut bacteria. These potential side effects may be uncomfortable, but are considered to be insignificant in the overall context of a promising therapy for an advanced tumor disease.

With regard to sulforaphane, its modus operandi is believed to be as an indirect antioxidant that helps to protect healthy cells from oxidative damage and reduce the short- and long-term harmful effects of cancer treatment [42]. However, concern has been raised that antioxidant supplements may also protect tumor cells during chemotherapy, thereby compromising treatment efficacy [42,43]. This has resulted in controversy over the guidelines for the use of vitamin supplements during cancer treatment. This issue was examined in an experimental human PDA xenograft model in mice. In this setup, sulforaphane did not protect tumor cells; instead, it increased the effect of gemcitabine, cisplatin, doxorubicin, 5-fluorouracil, sorafenib, and TRAIL [20,22,23,27].

In closing, the POUDER trial is the first clinical pilot trial to test the feasibility of an intake of freeze-dried broccoli sprouts as an additive of palliative chemotherapy in surgically non-resectable, advanced pancreatic cancer. Depending on the results of this pilot trial, a hypothesis for a confirmatory trial in the field will be generated and a consecutive RCT is planned.

## Trial status

The POUDER trial has been designed as a single center pilot randomized controlled trial (RCT). The initiation took place at the Department of Surgery, University of Heidelberg in December 2013 after approval by the local ethical committee.

## Abbreviations

AE: adverse event; ALDH1: aldehyde dehydrogenase isoform 1; CA 19-9: carbohydrate antigen 19-9; CEA: carcinoembryonic antigen; CRF: case report form; CSC: cancer stem cells; CT: computed tomography; HPLC: high performance liquid chromatography; MRI: magnetic resonance imaging; NF-κB: Nuclear factor-kappa beta; PDA: pancreatic ductal adenocarcinoma; PI: principal investigator; RCT: randomized controlled trial; SAE: serious adverse event.
